### Study population and eligibility

Patients will be recruited from the four participating psychiatric hospitals in Germany (Department of Psychiatry and Psychotherapy, University Hospital Carl Gustav Carus, Dresden; Municipal Hospital Dresden, Department of Psychiatry and Psychotherapy, Dresden; Department of Psychiatry, Psychotherapy and Psychosomatics University Hospital Halle; Department of Psychiatry and Psychotherapy Furtbach Hospital, Stuttgart). All patients meeting the inclusion criteria will be informed about the study. Inclusion criteria are 18 years of age and older, admitted as an inpatient, presenting with either a mood/affective disorder (F3 section of ICD-10) or schizophrenia, schizotypal or delusional disorder (F2 section of ICD-10) and written informed consent. Patients agreeing to participate in the study have a choice to which group they want to belong to. A randomised allocation is not made for ethical reasons. Patients with legal guardians are excluded from the study. Patients are not given any incentive or compensation for participation.

### Course

All patients receive a baseline visit (V0) during the week prior to discharge. At the baseline visit, data on demographics, substance use, psychiatric and medical history and treatment, history of suicidality, and family history of suicidality are documented.

In group 1, study contacts are scheduled at 6 (V6), at 12 (V12), and at 18 (V18) months after discharge from the psychiatric hospital. In group 2, more frequent study contacts are organised: During a period of 6 months after discharge, study visits are scheduled monthly (V1–V6), and subsequently every 2 months during the next period of 6 to 18 months after discharge (V8–V18). There will be a total of 3 study visits in group 1 and 12 study visits in group 2. The protocol (Fig. 1) accepts flexibility in terms of time, plus/minus 1 week, for study visits in the first 6 months after discharge, as well as a plus/minus 2 weeks tolerance for study visits V8 to V18. In case a patient gets admitted to a hospital while participating in the study, the course will be continued as conducted. Study visits include an evaluation of events that occurred between the study visits, e.g., stress-related events, inability to work, days of inpatient treatment, change or discontinuation of any treatment, and change of doctors, or therapists. Both baseline and study visit additionally includes several assessments recording symptomatology described in the next section.

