## Methods/design

The objective of this multi-centre trial is, firstly, to identify factors affecting suicide risk after psychiatric discharge and, secondly, to investigate whether a specific setting of care defined by regular personal contacts influences the elevated suicide risk after discharge from a psychiatric hospital.

This naturalistic study will allocate patients with schizophrenia, schizotypal and delusional disorders (ICD-10: F2), or mood disorders (ICD-10: F3) [15] as principal diagnosis either to a group with only a single contact 6, 12, and 18 months after discharge or to a group where personal contacts are organised monthly to every 2 months in the 1.5 years following discharge. These study contacts are an addition to treatment as usual for all patients and do not include medical or therapeutic treatment. Following discharge, the protocol will continue even if the patient gets admitted to the hospital again. By-phone visits will be allowed as alternatives.

The hypothesis to be tested is whether a specific setting of care reduces the suicide risk and does this particular setting of care plus regular treatment as usual lead to a significant reduction of suicidality compared to a less intense setting of care plus regular treatment as usual in the months following a psychiatric hospital stay.

The primary endpoint of the study is the evaluation of suicidality. Suicidality is measured by the score of the clinician-administered Sheehan Suicidality Tracking Scale (S-STS, [16]) at 6, 12, and 18 months after discharge.

Secondary endpoints include the score of the patient self-reported S-STS, changes in depressive symptoms as indicated by the Montgomery Asberg Depression Rating Scale (MADRS, [17]), changes in psychotic symptoms as indicated by the Brief Psychiatric Rating Scale (BPRS, [18]), and changes in the Visual Analogue Mood Scale (VAMS, [19]) at 6, 12, and 18 months after discharge. Due to the possibility of contacting the doctor/therapist and/or a close person of the patient in case of non-appearance to an appointment combined with failure, to reach the patient, we want to gain information about the state of health and ascertain possible suicides. At every study visit, it is asked for suicide attempts.

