**Fig. 1 Fig1:**
[figure not shown]
Trial flow

Both groups will receive treatment as usual in terms of regular meetings with their general practitioner, psychiatrist, and/or psychotherapist. The idea of the present study is to create a four eyes principle. The study setting includes an option to connect with the patients’ doctors or therapists as well as a person the patient chose in advance. It applies in case of health-related severe events (e.g., increasing suicide risk, suicide attempt). It enables the investigator to provide support, e.g., by coordinating further procedures with the patients’ psychiatrist/psychotherapist (provided that the patient voted for this option in written consent). If confronted with acute suicide risk, the investigator may also decide to follow the hospital’s emergency procedure in case of risk of self-harm and immediately present the participant to a psychiatrist on site. Connecting with doctors and therapists or a close person will also be possible in case of non-appearance to an appointment combined with a failure to reach the patient. This also allows us to gain important information on a potential suicide risk or suicide*.*

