### Statistical analysis

Descriptive statistics covering sociodemographic and clinical baseline data will be reported using proportions, means, and standard deviations as well as Chi-square tests, *t* tests, and Mann-Whitney tests as appropriate. Results will be presented with 95% confidence intervals where applicable. Proportions of adverse events will be summarised. Sociodemographic and clinical variables that differ significantly between groups at baseline will be included as covariates in further analyses. To identify potential explanatory variables on suicidality in the weeks and months after discharge, a potential correlation of variables will be assessed by frequencies, percentages, means and standard deviations, correlation coefficients, etc. Variables that are identified as potentially influencing suicidality will be included as factors in further analyses.

Normal distribution will be assessed by Shapiro-Wilk tests and by visual inspection of histograms. Homogeneity of variances will be assessed using Levene’s test.

Statistical tests will be two-sided using an alpha level of 0.05. All analyses will be conducted using IBM SPSS Statistics for Windows, version 25.

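### Suicide attempts and other events are collected with 6-month recall on 3 occasions in group 1 and 1- to 2-month recall on 12 occasions in group 2, so event ascertainment differs by group by design

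*Protocol article*

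**What the plan says.** The Course section of the protocol article sets the schedule. For group 1: "In group 1, study contacts are scheduled at 6 (V6), at 12 (V12), and at 18 (V18) months after discharge". Group 2 is seen monthly to month 6 and then every second month to month 18. The section gives the totals itself: "There will be a total of 3 study visits in group 1 and 12 study visits in group 2".

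The same section sets the reference period for events by the visit interval and not by the calendar: "Study visits include an evaluation of events that occurred between the study visits". Its examples are stressful events, time off work, inpatient days, changes to or stopping of treatment, and a switch of doctor or therapist. Methods/design adds for attempts: "At every study visit, it is asked for suicide attempts".

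Third parties can be contacted after a missed visit: "Connecting with doctors and therapists or a close person will also be possible in case of non-appearance to an appointment".

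The primary endpoint is defined separately, at visits that both groups share: "Suicidality is measured by the score of the clinician-administered Sheehan Suicidality Tracking Scale (S-STS, [16]) at 6, 12, and 18 months after discharge".

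On use of the data, Statistical analysis states "Proportions of adverse events will be summarised" and says that variables found to be potentially related to suicidality will enter later analyses as factors. Primary outcome measures places such risk factors in the ANCOVA. Secondary outcome measures lists Poisson and logistic regression among the methods for group comparisons.

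**The concern.** Visit frequency is what distinguishes the two groups, and it also sets how events are measured. At a shared visit, a question about the time since the last visit means something different in each group. Over the whole study, one group is asked four times as often and has to remember over a much shorter span. Missed-visit tracing follows the same pattern, with up to 12 scheduled triggers in group 2 against 3 in group 1.

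Two uses of the data are exposed. The first is any comparison between groups of attempts, inpatient days or other recalled events. The second is the primary ANCOVA, if an event variable such as stressful events after discharge is selected as a risk factor. A covariate measured differently in the two groups can itself shift the adjusted group difference. The limitations in the Discussion name self-chosen groups and the unobserved first days after discharge, but not this.

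**Working it through.** **Inputs.** The visit months come from the Course section, with discharge as month 0 and baseline V0 not counted. Intervals are nominal and ignore the visit tolerances of 1 or 2 weeks.

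- Group 1: 6, 12, 18.
- Group 2: 1, 2, 3, 4, 5, 6, 8, 10, 12, 14, 16, 18.

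**Step 1: reproduce the stated totals.** Group 1 has 3 visits. Group 2 has 6 (V1 to V6) + 6 (V8, V10, V12, V14, V16, V18) = 12. Both agree with the article.

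**Step 2: look-back at the shared visits.** Look-back = month of the visit minus month of the previous visit.

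| Visit | Group 1 | Group 2 | Ratio |
|---|---|---|---|
| V6 | 6 − 0 = 6 | 6 − 5 = 1 | 6:1 |
| V12 | 12 − 6 = 6 | 12 − 10 = 2 | 3:1 |
| V18 | 18 − 12 = 6 | 18 − 16 = 2 | 3:1 |

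**Step 3: coverage.**

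- Shared visits only: group 1 covers 6 + 6 + 6 = 18 of 18 months; group 2 covers 1 + 2 + 2 = 5 of 18, leaving 13 months uncounted.
- All visits: group 1 covers 18 months; group 2 covers 6 × 1 + 6 × 2 = 18 months.

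Total coverage is therefore equal when the interim records are used. What remains unequal is the length of recall and the number of inquiries.

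**Step 4: possible size if all visits are pooled.** The documents give no recall figures, so this step rests on an assumption: events occur at a constant rate, equal in both groups, and an event t months before the visit is reported with probability exp(−kt). The share reported from an interval of length L is (1 − exp(−kL))/(kL). Averaged over 18 months:

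- Group 1: 3 × (1 − exp(−6k))/k ÷ 18.
- Group 2: [6 × (1 − exp(−k))/k + 6 × (1 − exp(−2k))/k] ÷ 18.

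| k per month | Group 1 | Group 2 | Group 2 / group 1 |
|---|---|---|---|
| 0 | 1.000 | 1.000 | 1.000 |
| 0.02 | 0.942 | 0.984 | 1.044 |
| 0.05 | 0.864 | 0.960 | 1.111 |
| 0.10 | 0.752 | 0.921 | 1.225 |

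At the same true rate, group 2 would record from 0% to about 22% more events over this range of k.

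**Step 5: direction.** Pooled records tend to raise the count in group 2. Shared-visit records alone lower it. The sign depends on how interim records are combined, which the article does not state and the analysis plan, not shown, may settle. The unequal collection is fixed by the protocol text either way.

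**The case against.** **The primary score.** A reader might infer that the S-STS at V6, V12 and V18 also covers 6 months in group 1 and 1 or 2 months in group 2. The article does not support that. The between-visit inquiry has its own list of examples, and the Course section then says that visits also include the symptom scales, which the Assessments section describes. No S-STS reference period is given. It may lie in the instrument or the rater instructions, and a condensed article may leave it there. This part of the objection stands.

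**A several-fold distortion.** A reader might compute that, at an assumed constant risk of 2% per month, a 6-month window captures 1 − 0.98^6 = 11.4% of patients, against 2.0% for 1 month and 4.0% for 2 months. At 5% per month the figures are 26.5% against 5.0% and 9.8%, so the ratio is about 3 to 6 with no true effect. That arithmetic needs either an S-STS rated since the last visit or group 2's interim event records thrown away. The article states neither, so the figure does not describe a planned analysis.

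**Other stronger readings.** The article does not plan predictor analyses that pool every visit; its stated scale comparisons are at 6, 12 and 18 months. Nor does it follow that more suicides would be found in group 2. Tracing applies to both groups, and a death in group 1 would normally surface at the next missed visit, so mainly the timing of detection differs. For adverse events, only a summary of proportions is stated.

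**Unequal contact is the intervention.** This is true, and the Discussion presents closer recognition of suicidal tendencies as part of how the setting may work. Unequal contact does not, however, require a different event question at the shared visits.

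**Conclusion.** The point holds for recalled events: attempts, inpatient days, stressful events and treatment changes. The stated collection rule gives 3 inquiries with 6-month recall in group 1 and 12 inquiries with 1- or 2-month recall in group 2, over the same 18 months. This follows from the schedule alone and needs no assumption.

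The effect on counts does need one. With a decay rate between 0 and 0.10 per month and equal constant event rates, pooled records would show 0% to about 22% more events in group 2; with no decay the excess is zero. If only shared-visit records were used, 13 of group 2's 18 months would be missing.

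The consequence is limited to secondary event comparisons and to any event variable taken into the ANCOVA as a risk factor. It is not shown for the primary S-STS score. In a study described as a pilot, this is worth correcting and disclosing, but the trial's main comparison does not stand or fall by it.

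**What to change.** - At V6, V12 and V18, ask both groups one identical question about the preceding 6 months for attempts, admissions and stressful events. Add it beside the existing question about the time since the last visit, so that no current item changes meaning during the study.
- Base between-group event comparisons, and any event covariate in the ANCOVA, on these common records for months 0–6, 6–12 and 12–18. Use group 2's interim records descriptively or in a sensitivity analysis.
- For data already collected (recruitment began in 2018), sum group 2's interim records into the same three intervals and add the difference in recall and in number of inquiries to the limitations.
- Confirm in the rater instructions that the S-STS reference period is the same in both groups at the shared visits.

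**Cost.** One extra question for group 2 at three visits, a line in the case report form and some wording in the plan; no new visits. The main comparison gives up some of group 2's finer recall. The change does not remove the problem fully, because patients asked at interim visits have rehearsed their answers.

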**Fig. 1 Fig1:**
[figure not shown]
Trial flow

Both groups will receive treatment as usual in terms of regular meetings with their general practitioner, psychiatrist, and/or psychotherapist. The idea of the present study is to create a four eyes principle. The study setting includes an option to connect with the patients’ doctors or therapists as well as a person the patient chose in advance. It applies in case of health-related severe events (e.g., increasing suicide risk, suicide attempt). It enables the investigator to provide support, e.g., by coordinating further procedures with the patients’ psychiatrist/psychotherapist (provided that the patient voted for this option in written consent). If confronted with acute suicide risk, the investigator may also decide to follow the hospital’s emergency procedure in case of risk of self-harm and immediately present the participant to a psychiatrist on site. Connecting with doctors and therapists or a close person will also be possible in case of non-appearance to an appointment combined with a failure to reach the patient. This also allows us to gain important information on a potential suicide risk or suicide*.*

### Assessments

#### Clinician-administered scales

Sheehan Suicidality Tracking Scale (S-STS, [20]) is used to assess suicidal thoughts and/or behaviour, both clinician and self-reported. Items of the S-STS are scored on a 5-point Likert scale (0 = not at all, 1 = a little, 2 = moderately, 3 = very, and 4 = extremely). The Montgomery Asberg Depression Rating Scale (MADRS, [16]) will assess depressive symptoms; the Brief Psychiatric Rating Scale (BPRS, [17]) assesses psychotic symptoms. Investigators will also make use of the AMDP-rating scale to evaluate clinical psychopathology (Arbeitsgemeinschaft für Methodik und Dokumentation in der Psychiatrie, AMDP [19]). A rater training, as well as an evaluation of inter-rater reliability, was held at the beginning of the study to minimise differences between investigators and centres.

#### Patient-administered scales

The self-rating version of S-STS will be used as a self-rating instrument on suicidality. The Visual Analogue Mood Scale (VAMS) [18] will be used to reflect the current subjective mental state. Both will be applied at baseline contact and at each following contact in both groups. At the baseline visit only (V0), patients of both groups will be asked to complete a questionnaire on perfectionism [21–24], as well as the FPI-R Questionnaire (Freiburger Persönlichkeitsinventar, [25]) to investigate whether and to what extent various psychological constructs (e.g., perfectionism, aggressiveness) are associated with suicidality. Additionally, we ask patients to fill out the Resilience Scale (RS13) [26] to investigate possible influences on the development of suicidality. The RS13 measures resilience on a 7-point scale and is the short German version of the RS-25 from Wagnild and Young [27].

### Power analysis and sample size calculation

The presented multi-centre trial is designed as a pilot study. We, therefore, did not conduct a statistical power analysis or sample size calculation. Yet, we estimate a minimum of 300 patients treated with ICD-10 F2- or F3-diagnosis in each study centre every year. Based on clinical experience, we strive for at least 100 patients per study centre.

### Statistical analysis

Descriptive statistics covering sociodemographic and clinical baseline data will be reported using proportions, means, and standard deviations as well as Chi-square tests, *t* tests, and Mann-Whitney tests as appropriate. Results will be presented with 95% confidence intervals where applicable. Proportions of adverse events will be summarised. Sociodemographic and clinical variables that differ significantly between groups at baseline will be included as covariates in further analyses. To identify potential explanatory variables on suicidality in the weeks and months after discharge, a potential correlation of variables will be assessed by frequencies, percentages, means and standard deviations, correlation coefficients, etc. Variables that are identified as potentially influencing suicidality will be included as factors in further analyses.

Normal distribution will be assessed by Shapiro-Wilk tests and by visual inspection of histograms. Homogeneity of variances will be assessed using Levene’s test.

Statistical tests will be two-sided using an alpha level of 0.05. All analyses will be conducted using IBM SPSS Statistics for Windows, version 25.

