#### Primary outcome measures

Group comparison of suicidality measured by the score of the clinician-administered Sheehan Suicidality Tracking Scale will be conducted using analysis of covariance (ANCOVA). Baseline variables that differed significantly between groups, as well as potentially influencing risk factors, will be included in the analysis.

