#### Secondary outcome measures

Group comparisons of secondary outcome measures will be conducted using analysis of (co)variance (AN(C)OVA), Poisson regression, logistic regression, *t* tests, Chi-square tests, or non-parametric methods as appropriate. The course of suicidality measured with S-STS, as well as scores of the other scales, will be analysed within groups using repeated measures AN(C)OVA for both groups separately comparing baseline values with scores at 6, 12, and 18 months.

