The present study has several limitations. First, patients with a principal diagnosis of only categories F2 and F3 of ICD-10 (schizophrenia, schizotypal or delusional disorders, depression, bipolar disorder) will be included. In contrast, all other diagnoses will be accepted as comorbidities only. This procedure leaves out several groups of patients. We tried to restrict the heterogeneity of our study population in favour of receiving insights that are more meaningful for a well-defined group of patients at this first step of approaching very critical aspects of suicidality. Second, a bias may arise from the fact that patients have a choice of which group they would like to be placed in, either group 1 or group 2. On the other hand, this choice can offer useful insights into real-world clinical aspects by reflecting patients’ different characteristics as well as needs and motivation to make use of suicide prevention measures providing personal contact. This is in line with the ethical requirements of not withholding any condition from participants.

As a limitation of our study, we do not examine developments during the first days after discharge. The first study contact is scheduled 1 month after discharge. A recently published meta-analysis comprising 34 publications showed a pooled estimate of the suicide rate of 2950 suicides per 100,000 person-years (95% CI = 1740–5000) [28]. The pooled estimate of the suicide rate during the first month after discharge was 2060 per 100,000 person-years (95% CI = 1300–3280).

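### Patients choose their group, yet the primary ANCOVA's covariates are picked from the trial's own data by baseline p-values and an open-ended screen, with no confounder set fixed, not even baseline S-STS

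*Protocol article*

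**What the plan says.** There is no randomisation. Under Study population and eligibility the article says "Patients agreeing to participate in the study have a choice to which group they want to belong to" and "A randomised allocation is not made for ethical reasons". The Discussion concedes that "a bias may arise from the fact that patients have a choice of which group they would like to be placed in".

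Covariates reach the between-group models by two routes, both set out under Statistical analysis:

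- **Route 1, baseline significance:** "Sociodemographic and clinical variables that differ significantly between groups at baseline will be included as covariates in further analyses".
- **Route 2, association with suicidality:** "a potential correlation of variables will be assessed by frequencies, percentages, means and standard deviations, correlation coefficients, etc", after which "Variables that are identified as potentially influencing suicidality will be included as factors in further analyses".

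The section Primary outcome measures repeats both routes for the ANCOVA on the clinician-administered S-STS: "Baseline variables that differed significantly between groups, as well as potentially influencing risk factors, will be included in the analysis". Tests are two-sided at 0.05. Baseline S-STS, centre and diagnosis group (F2 or F3) are not named as covariates of that model. Baseline scores do appear under Secondary outcome measures, but in the repeated-measures analyses run within each group separately. For secondary between-group comparisons the menu runs from AN(C)OVA and regression to t tests and "Chi-square tests, or non-parametric methods as appropriate".

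**The concern.** When patients select their own group, the covariates largely decide whether the group difference reflects the contacts or the kind of patient who asked for more of them. A baseline test is a poor way to choose them. Its p-value depends on the imbalance and the sample size. The bias that a variable causes depends on the imbalance and on how strongly the variable predicts the outcome. Several variables that each miss significance can still add up to a material bias.

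Route 2 does look at prognosis, but it has no threshold and is applied once outcome data are in hand. It is also not confined to variables measured before discharge. The Methods/design section records hospital days, medication, psychotherapy sessions and stressful events after discharge. More frequent contacts may change some of these, and adjusting for a consequence of the contacts can remove part of a real effect.

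**Working it through.** The article gives no power or sample size figure to reproduce. The total of 4 centres x 100 patients = 400 comes from its stated target. Group split, imbalances and correlations below are assumptions, because the article gives none.

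**1. How often the baseline test flags a true imbalance**

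For an imbalance of d standard deviations and group sizes n1 and n2, the standard error is SE = sqrt(1/n1 + 1/n2). The chance of p<0.05 is Φ(d/SE − 1.96) + Φ(−d/SE − 1.96), and the second term is negligible here.

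| Split of 400 | SE | d = 0.15 | d = 0.20 | d = 0.30 |
|---|---|---|---|---|
| 200/200 | 0.100 | Φ(1.50 − 1.96) = 32% | 52% | Φ(3.00 − 1.96) = 85% |
| 120/280 | 0.109 | Φ(1.375 − 1.96) = 28% | 45% | Φ(2.75 − 1.96) = 79% |
| 80/320 | 0.125 | Φ(1.20 − 1.96) = 22% | 36% | Φ(2.40 − 1.96) = 67% |

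The imbalance flagged with 80% probability is (1.96 + 0.84) x SE, that is 0.28, 0.31 and 0.35 SD. Imbalances of 0.2 SD or less are missed about half the time or more. Those of 0.3 SD or more are mostly caught.

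**2. What the two routes do together**

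The simulation has N = 400 (200/200 and 300/100), no true group effect, independent confounders each imbalanced by 0.15 SD, and outcome SD 1 within groups. With no adjustment the bias is (number of confounders) x 0.15 x slope. That is 5 x 0.15 x 0.3 = 0.225 SD for five confounders with slope 0.3. For ten with slope 0.15-0.20 it is 0.225-0.30 SD.

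| Rule | Confounders | Bias (SD) | Type I error |
|---|---|---|---|
| Fixed set, all included | five, slope 0.3 | about 0 | about 5% |
| Both routes, screen at p<0.05 | five, slope 0.3 | about 0 | about 5% |
| Both routes, screen at \|r\|>0.3 | five, slope 0.3 | 0.04-0.05 | about 8% |
| Both routes, screen at \|r\|>0.3 | ten, slope 0.15-0.20 | 0.10-0.15 | 15-26% |

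The reason is simple. At N = 400, p<0.05 corresponds to |r| above about 1.96/sqrt(400) = 0.098, so a confounder correlated 0.15-0.30 with the outcome nearly always passes. A cut at |r|>0.3 stops about half of those with slope 0.3 and almost all the weaker ones, which leaves them to route 1.

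**3. Post-discharge variables**

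In an illustrative extreme case, where the whole effect of the contacts ran through one recorded post-discharge variable, adjusting for that variable turned a true effect of −0.25 into 0.00. A partial pathway would remove only part of the effect.

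**The case against.** The strongest defence is that significance at baseline is not the only way in. A reader might infer from the first rule that a strong predictor without a significant imbalance is dropped, or that most real confounders go unadjusted. The documents do not support either reading. Both sections also admit variables thought to influence suicidality, and prior suicidality and baseline S-STS are natural candidates. With a p<0.05 screen the simulated bias disappears. Route 1 alone would give a bias of 0.10-0.12 SD and a type I error of roughly 16-19% with five confounders, but that is not the rule the article describes. Nor can it be said that most confounders are missed, because the actual imbalances are unknown and large ones are usually flagged.

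A reader might also infer that secondary outcomes will be compared without adjustment. The article lists adjusted models beside the simple tests, to be used as appropriate, and applies the covariates to further analyses in general.

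Finally, this is a pilot study, it discloses the self-selection bias, and a condensed article may leave the exact covariate list to a fuller document. All of that is fair, and a missing list is not the point here. What remains is that the article states a selection rule, and the rule is a poor one. Pilot status does not remove this, since the Methods/design section sets out a hypothesis of a significant reduction in suicidality.

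**Conclusion.** The point holds in a limited form. The primary model's covariates are chosen from the trial's own data by a baseline significance test and an open-ended screen, in a comparison where patients choose their group. Whether the test keeps its 5% level depends on a threshold that the article does not state. Under assumed 0.15 SD imbalances and about 400 patients, type I error ranges from about 5% to 15-26%, and bias from about 0 to 0.10-0.15 SD. These figures illustrate sensitivity to the rule. They do not forecast this trial's error rate. Baseline S-STS is measured and would probably pass most screens, but nothing guarantees that it is in the model. As worded, the screen could also bring post-discharge variables into the group comparison, although the article does not say that it will.

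**What to change.** - Delete the significance-based rule under Statistical analysis and under Primary outcome measures.
- Fix in advance one set of V0 variables chosen on subject-matter grounds: baseline S-STS, MADRS, BPRS, prior suicidality, F2 versus F3, centre, age and sex. Include them whatever their baseline p-value.
- Use the same set in the primary ANCOVA and in the adjusted secondary between-group comparisons.
- Keep post-discharge variables out of the group-effect model. The screen for influences on suicidality belongs in the separate risk-factor analysis, which is the study's first objective.
- Word the group result as an adjusted association.

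Propensity weighting on the same set, and standardised differences in place of baseline tests, are optional additions. The cost is plan wording and a few degrees of freedom out of about 400. No new data are needed.
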